# A protocol for a single-center, single-blinded randomized-controlled trial investigating volar plating versus conservative treatment of unstable distal radius fractures in patients older than 65 years

**DOI:** 10.1186/s12891-019-2677-y

**Published:** 2019-06-29

**Keywords:** Distal radius fractures, Volar plating, Conservative, Complications, Functional outcome, Elderly

## Abstract

**Background:**

Distal radius fractures (DRF) are very common in elderly patients, who present at the Emergency Department. Surgical treatment with open reduction and internal fixation using volar locking plates is widely prevalent despite the lack of evidence proving its superiority to conservative treatment with closed reduction and plaster immobilization. The purpose of this study is to investigate whether conservative treatment is superior to volar plating in terms of number of complications and results in a comparable or superior functional outcome in patients ≥65 years.

**Methods:**

In this single-center, single-blinded randomized-controlled trial, patients ≥65 years with distal radius fractures will be invited to participate. A total of 50 patients per treatment arm is required to provide 80% statistical power at a 5% alpha level assuming a difference of 20% in complication rate between operatively and conservatively treated patients. Primary outcome measures will be complication rate, Quick DASH score (Quick Disabilities of the Arm, Shoulder and Hand), PRWE (Patient rated Wrist evaluation), and range of motion of the wrist. Secondary outcome measures will be grip strength, pinch gauge, pain, use of pain medication EQ5D score (European Quality of life – 5 dimensions), standardized radiographs. One year of follow-up is planned with data collection at the day of injury, after 2 weeks, after 5 weeks, after 6 months, and after 12 months. An intention-totreat and per-protocol analysis will be performed.

**Discussion:**

This prospective trial helps to clarify the best treatment strategy for displaced DRF patients ≥65 years.

**Trial registration:**

This trial is approved by the Danish Scientific Ethical Committee (ID: 1–10–72-420-17) and registered at Clinicaltrials.gov (Trial registration number NCT03716661).

## Background

Distal radius fractures (DRF) account for 18% of all fractures in the elderly ≥65 years of age [1]. The estimated lifetime risk for DRF is 15% for females and 2% for males [2]. The incidence rate is 190–200 per 100,000 person-years [3]. DRF is associated with osteoporosis, hence the age-related incidence rate increases almost 3-fold from the age of 60 to 99 in women [1, 4, 5]. In Europe, the proportion of the elderly population is estimated to increase by 56% in men and by 41% in women until 2035 [6, 7]. Consequently, the need to clarify the best treatment strategy for DRF in elderly is evident.

In recent years, there has been a trend to treat DRF patients that require surgical treatment with an open reduction and internal fixation (ORIF) using a volar locking plate. The Danish Health Authority stipulates in the National Clinical Guidelines (NCG) regarding the treatment of low-energy DRF [8] to volar plate fractures that fulfill the following radiologic criteria after attempted closed reduction:> 10° dorsal tilt of the radius in relation to perpendicular to the longitudinal axis of radius> 2 mm articular step-off> 2 mm ulnar varianceincongruence of the distal radioulnar jointsubstantial dorsal comminution indicating gross instability

If one or more of these criteria are met, ORIF most often utilizing a volar locking plate is advised regardless of the patient’s age. The guideline also highlights that conservative management should be considered in patients with low functional demands.

Notably, the guideline does not include recommendations for high-energy, open fractures nor grossly instable fractures: volarly displaced (Smith), radial styloid (Cheuffeur) or articular rim (Barton) fractures. However, most of these fractures are also treated with volar locking plates in Denmark.

The radiological NCG criteria rely on clinical observations only and have not been systematically evaluated prospectively. Furthermore, the reliability of the radiological criteria has been questioned [9]. Therefore, The Danish Health Authority evaluates that the recommendations for treating DRF primarily are based on low quality evidence and must be considered as “good practice”-guidelines.

Volar plating of DRF may harm patients. Complication rates of up to 33% have been reported in surgically treated DRF patients [10–14]. Our own estimation of the complication rate after volar plating of DRF is 14.6% [95% CI 11.8–17.7%] in a retrospective cohort of 595 patients with 3.2 years follow-up [3]. This high complication rate is not insignificant for the patients. Neurologic disturbances, tendon irritation and rupture, infection, etc. often lead either to a re-operation or an increase in out-patient visits and may result in permanent morbidity and impaired function [15].

Furthermore, volar plating improves the early functional recovery, but long-term functional results are similar with other treatment modalities in patients ≥65 years [16]. However, volar plating is still the gold standard in the treatment of DRF in adults regardless of age.

An increase in complications with no clinically significant difference between the functional outcome of operatively and conservatively treated patients was demonstrated [16, 17]. Furthermore, the patients treated operatively had a higher complications rate than the conservatively treated patients [17]. In addition, patients with DRF treated nonoperatively have shown to have less pain and better or equal wrist function after a 1 year follow-up than those treated surgically [18]. A Danish review of operatively treated patients suggest a more restrictive choice of treatment for DRF amongst the elderly than the NCG stipulate [2]. All things considered, no existing evidence proves the benefit of treating DRF operatively in the elderly.

Here, we question whether the potential benefit of volar plating, namely an earlier functional recovery outweighs the risk of encountering a complication. Especially in the light of retired patients (≥ 65 years), where return to work is not a burning issue, it seems worthwhile to investigate this issue both in the interest of the patients and society.

### Research hypothesis

Patients above 65 years of age, who sustain a DRF that fulfill the national radiologic criteria for operative treatment will experience fewer complications when treated with dorsal plaster cast immobilization only than when operated using a volar locking plate.

Meanwhile, the secondary outcome measures will be comparable and below the clinically relevant difference – e.g. a mean difference in the Danish version of the Quick Disabilities of the Arm, Shoulder and Hand (Quick DASH) below 16–20 point [19–22].

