## Methods/design

### Study design

A prospective single-center, single-blinded randomized-controlled superiority trial with two parallel treatment arms and a third control arm (Fig. 1);Arm 1: volar plating, 2-weeks dorsal plaster cast followed by 3-weeks orthosis immobilization with a single hand therapeutic instruction;Arm 2: closed reduction and 5-weeks dorsal plaster cast immobilization with a single hand therapeutic instruction;Arm 3: a control group of patients with minimally displaced DRF that do not fulfill the radiologic criteria.

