#### Primary outcomes

The complication rate will be estimated at day 0, 2 weeks, 5 weeks, 6 months, and 12 months after the injury.

Complications are defined as the presence of:Sensory disturbance, including carpal tunnel syndrome and chronic regional pain syndromeFlexor tendon rupture and irritationExtensor tendon rupture and irritationHardware failure, e.g. osteosynthesis looseningInfection: superficialInfection: deepReoperation with hardware replacementReoperation with hardware removal (partial or total), which is not routinely performed in DenmarkVascular compromised (capillary refill ≥2 s)

Patients will report complications at the given timepoints by answering a questionnaire stating either yes / no and a free-text explanation. If the patient states any complications, a member of the research group will qualify the answer and fill in the free text. However, a YES can only be qualified and shall never be erased if the physician does not agree with the patient’s opinion or explanation.

The Danish version of the Quick Disabilities of the Arm, Shoulder and Hand [22] will be used to assess the level of functionality prior to injury, after 2 weeks, 5 weeks, 6 months, and 12 months. The minimal clinically relevant difference is 16 to 20-point difference in Quick DASH [19–21].

Range of motion is measured by a registered nurse using a goniometer. To ensure the observer is blinded, the patient is instructed not to talk about the treatment. Furthermore, all wrists will be covered by a glove concealing potential scares (Fig. 3). The following data are thus collected in a blinded fashion wrist flexion, extension, pronation, supination, radial deviation, ulnar deviation. The contralateral side will serve as a reference and history of injuries or operations of the contralateral side will be recorded.

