#### Statistical analysis plan

That data will be analyzed using Fisher’s exact test and Mann Whitney U test. The desired applied statistic is odds ratio with Pearson’s 95% confidence interval. Should any data be lost in the follow-up, the Last Observation Carried Forward concept will be used. Treatment arm 3 will be analyzed after 6 months follow-up and published separately.

All test will be two-tailed and assessed at the 5% alpha level. Categorical measures will be presented as percentages. An intention-to treat and per-protocol analysis will be considered. Continuous measures will be presented as means with standard deviations and medians with inter-quartile range. Treatment effects over time will be assessed using linear mixed effect models with patient treated as random factor. A normal distribution with an identity link function will be assumed for continuous measures, while a multinomial distribution and cumulative logit function will be applied to ordinal outcomes.

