## Discussion

This prospective trial helps to clarify the best treatment strategy for displaced DRF patients ≥65 years. Practical limitations prevent the conduction of a double-blinded data collection, as no sham operations will be performed.

To the best of our knowledge, only one similar randomized controlled trial investigating volar locking plates versus conservative treatment in patients ≥65 years with DRF has been conducted [8, 16]. In 2011, Arora and co-workers reported similar results in terms of patient-reported outcome measures DASH and PRWE, pain level and range of motion between 36 operatively and 37 non-operatively treated patients [16], while the complication rate was 36 and 14% in the two groups, respectively. However, this trial did not have a significant clinical impact on the treatment of this patient group in Denmark. In the light of these promising initial report limiting the need of surgical intervention, there is a need to verify its results. Thus, the current trial will help to clarify the best treatment strategy for displaced DRF in patients ≥65 years in terms of complication rate and expected comparable functional outcome. If the results of the study indicate one treatment superior to the other, clinical guidelines are likely to be influenced by the current study.

Furthermore, cost effectiveness calculations can be performed on the basis of results of the current study and unnecessary operations may be prevented in order to live up to the Hippocratic oath, ‘primum non nocere - first do no harm’.

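### Comparable function is part of the aim, but the protocol attaches no comparability criterion to it: the Quick DASH threshold is a range, no visit is fixed, and no confidence limit is tied to a margin.

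*Protocol article*

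**What the plan says.** Comparable function appears in three places in the protocol article. The abstract's Background asks whether cast treatment has fewer complications than plating and "results in a comparable or superior functional outcome in patients ≥65 years". The Research hypothesis states that "the secondary outcome measures will be comparable and below the clinically relevant difference", with a mean Quick DASH difference under 16 to 20 points as the example. The Discussion says the trial will clarify the best treatment "in terms of complication rate and expected comparable functional outcome" and that guidelines are likely to be influenced.

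The threshold is repeated under Primary outcomes: "The minimal clinically relevant difference is 16 to 20-point difference in Quick DASH". It is not called a non-inferiority or equivalence margin. Quick DASH is scored for the pre-injury state and at 2 weeks, 5 weeks, 6 months and 12 months.

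Study design calls the trial a "single-blinded randomized-controlled superiority trial". The Statistical analysis plan section names Fisher's exact and Mann-Whitney U tests, an odds ratio with a 95% interval, and linear mixed models for treatment effects over time. It adds: "All test will be two-tailed and assessed at the 5% alpha level". The sample size rests on complications alone.

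**The concern.** The aim has two parts: fewer complications with the cast, and function that is not worse by a relevant amount. The second part is in substance a non-inferiority claim, which needs an interval for the difference that excludes a relevant loss. The protocol does not say how it will be judged, and what it does fix leaves three gaps:

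- **Test.** A two-tailed difference test addresses whether the arms differ, not whether a relevant loss is excluded. Mann-Whitney U does not estimate the mean difference in which the hypothesis is framed.
- **Threshold.** 16 to 20 is a range. A result between the two ends passes or fails according to the end chosen.
- **Visit.** There are four post-injury visits. The protocol's own Background says plating speeds early recovery while long-term results are similar, so the answer may depend on the visit.

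At stake is the message that would influence guidelines: fewer complications at no functional cost. As written, margin and visit could be settled after the results are known.

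**Working it through.** **Plan's own figure.** There is none for function. The only sample size figure, 49 per arm, concerns a 20-point difference in complication rate, and the arm rates are not given. It is reproduced by 25% versus 5%: [1.96·√(2·0.15·0.85) + 0.8416·√(0.25·0.75 + 0.05·0.95)]² / 0.20² = (0.990 + 0.408)² / 0.04 = 48.8, hence 49. It carries no information on Quick DASH.

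**Inputs.** 50 per arm (Randomization); thresholds 16 and 20 (Research hypothesis; Primary outcomes). The SD of Quick DASH is not in the document, so 20, 25 and 30 are assumed. Differences are cast minus plate, positive meaning worse function with the cast. Dropout is ignored at first.

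**Standard error and interval.** SE = SD·√(2/50) = 0.2·SD. The 95% half-width is 1.984·SE (t with 98 degrees of freedom).

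| Assumed SD | 20 | 25 | 30 |
|---|---|---|---|
| SE | 4.0 | 5.0 | 6.0 |
| Half-width | 7.9 | 9.9 | 11.9 |
| (a) True loss 16 is non-significant: Φ(1.984 − 16/SE) | 2% | 11% | 25% |
| (b) Highest upper limit with a non-significant result: 2 × half-width | 15.9 | 19.8 | 23.8 |
| (c) True loss 16, observed difference below 16 | 50% | 50% | 50% |
| (d) True loss 16, observed difference below 20: Φ(4/SE) | 84% | 79% | 75% |
| (e) Power of a confidence-limit rule at margin 16, true difference 0: Φ(16/SE − 1.984) | 98% | 89% | 75% |

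**Reading the rows.**

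- Rows (a) and (b): what non-significance means depends on an SD the plan does not state. At SD 20 a non-significant t-type result always has an upper limit below 16. The boundary is 2·1.984·0.2·SD = 16, so SD = 20.2. At SD 25 such a result excludes 20 but need not exclude 16. At SD 30 it need not exclude either.
- Rows (c) and (d): if only the observed mean difference were read against the range, moving from 16 to 20 would raise the pass rate for a true 16-point loss from 50% to between 75% and 84%.
- Row (e): power stays at 80% while 16/(0.2·SD) − 1.984 ≥ 0.842, that is, SD ≤ 28.3.

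**Dropout check.** With 40 per arm, as an illustration, SE = 0.2236·SD and t = 1.991. Row (e) becomes 94%, 81% and 65%.

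**The case against.** Several stronger readings are tempting, and the documents do not support them.

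- *A reader might infer that only difference tests are planned.* Linear mixed models with an identity link are also planned, and they can give the mean difference with its interval. The estimator is there; the criterion is not.
- *A reader might infer that non-significance can never support comparability.* At an SD of about 20 or less with 50 per arm, a non-significant t-type result would itself exclude 16 points. The objection has force at larger SDs, and for a reading that rests on Mann-Whitney U.
- *A reader might infer that the plan will compare a bare point estimate with 16 or 20, or report non-significance as comparability.* The document says neither. The Research hypothesis states an expectation about the true difference. Rows (c) and (d) show what such a reading would do, not what the plan prescribes.
- *A reader might count non-significance at a smaller true loss, say 10 points, as a false claim.* Ten points lies below the plan's own relevance threshold, so the relevant error is at 16. Likewise, a significant but small difference is not a flaw, because the stated threshold allows it to be interpreted.

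It can also be said that the superiority label is correct for complications, that the hypothesis calls function secondary, and that reading an interval against a margin is often left to a fuller document. This lowers the severity. It does not remove the point, because the protocol itself fixes a range and two-tailed testing beside a comparability hypothesis, and a fuller plan that followed this text would inherit the mismatch. The abstract and the Primary outcomes section also list Quick DASH as primary; that inconsistency is a separate matter.

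**Conclusion.** The point holds as a gap in the decision rule, not in the sample size or the choice of model; it should be fixed. Comparable function is a stated aim, yet no single margin, visit or confidence-limit criterion supports it. With 50 per arm, a true 16-point loss would go undetected by a two-tailed t-type test in about 2%, 11% or 25% of trials at SD 20, 25 or 30. The open choice between 16 and 20 can change the conclusion on its own.

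All figures except the 50% in row (c) rest on the assumed SD. They use a simple two-sample comparison as an approximation to the mixed model and make no allowance for dropout, except where 40 per arm is stated.

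**What to change.** Before the data are seen, add to the Research hypothesis and Statistical analysis plan sections:

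1. One margin from the plan's own range. Sixteen is the stricter end; the essential step is to name one.
2. One primary time point for the functional claim, for example 12 months.
3. The rule: function with the cast is called comparable only if the upper limit of the two-sided 95% confidence interval for the mean Quick DASH difference (cast minus plate), from the planned mixed model, is below the margin in both the intention-to-treat and the per-protocol sets. The abstract says both analyses will be done, while the Statistical analysis plan section only considers them; this should be made firm.
4. A statement that a non-significant difference will not be reported as comparability.

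The one-sided form suits the abstract's aim of comparable or superior function. If equivalence in both directions is meant, the whole interval must lie within ±16. Power, 2Φ(16/SE − 1.984) − 1, is then 96%, 78% and 50% at SD 20, 25 and 30, and 80% is kept only up to an SD of about 24.

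The cost is a few sentences. Under the one-sided rule no more patients are needed for an SD up to about 28, before dropout. The downside for the sponsor is a stricter criterion fixed in advance: with 50 per arm, the observed difference would have to be below about 8, 6 or 4 points (16 minus the half-width) at SD 20, 25 or 30.

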## Methods/design

### Study design

A prospective single-center, single-blinded randomized-controlled superiority trial with two parallel treatment arms and a third control arm (Fig. 1);Arm 1: volar plating, 2-weeks dorsal plaster cast followed by 3-weeks orthosis immobilization with a single hand therapeutic instruction;Arm 2: closed reduction and 5-weeks dorsal plaster cast immobilization with a single hand therapeutic instruction;Arm 3: a control group of patients with minimally displaced DRF that do not fulfill the radiologic criteria.

**Fig. 1 Fig1:**
[figure not shown]
Study Design. An overview of the study design showing the 3 arms. *These radiographs are evaluated respectively after study completion and do not influent the prospective follow-up of the individual patient

Follow-up time is planned to be 1 year with out-patient visits at 2 weeks, 5 weeks, 6 months and 12 months after the injury. This trial is approved by the Danish Scientific Ethical Committee on the 3rd of September 2018. This study is carried out at the Regional Hospital Randers, Denmark with a coverage area of approximately 270,000 inhabitants.

### Eligibility criteria

All patients with DRF diagnosed at the emergency department are screened for eligibility.

#### Intervention groups: (arm 1 and arm 2)

Eligibility criteria for participants who will be allocated to random treatment are:≥ 65 years oldlow-energy distal radius fracture.

The distal radius fracture must fulfill at least *one* of the following radiological criteria after closed reduction in the emergency department in order to be randomized between treatment arm 1 and 2:> 10° dorsal tilt of the radius in relation to perpendicular to the longitudinal axis of radius> 2 mm Ulnar variance> 2 mm Articular step-offIncongruence of the distal radioulnar jointSubstantial dorsal comminution< 20° Radial inclination< 5 mm Radial length

#### Control group: (arm 3)

Eligibility criteria for participants in the control group, arm 3:≥ 65 years oldlow-energy distal radius fracture.

This distal radius fracture had to fulfill *all* the following radiologic criteria:≤ 10° Dorsal tilt of the radius in relation to perpendicular to the longitudinal axis of radius≤ 2 mm Ulnar variance≤ 2 mm Articular step-offNo incongruence of the distal radioulnar joint≥ 20° Radial inclination≥ 5 mm Radial length

### Exclusion criteria

Patients < 65 yearshigh-energy fractureopen fractureconcomitant injuries, e.g. multiple fractures on afflicted armnot capable of giving written consentprevious DRF or forearm fracture on the same side

### Recruitment

Any participant must be approved eligible for the study by either one of the consultants in the research group or the house physician on call. Patients are primarily recruited by directly contact in the emergency room on the day of primary contact, where they are informed about the study and asked for written consent. The Danish consent form and patient information material is given to the patient, a blank sample can be ordered from the corresponding author. Every patient who is treated in the emergency department during a shift is discussed the following day on a conference, where all radiographs also are reviewed. This additional control ensures that every potential participant is assed for eligibility and offered enrollment in the study either directly in the emergency room or the day after by telephone. When recruitment is done over the telephone, written consent is obtained before surgery or at the 2 week out-patient visit, if the participant should be randomly assigned to conservative treatment or if the patient is in the control group. The recruiting health care personnel randomly assigns participants to the interventions as described below.

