### Randomization

Randomization is executed by random drawing of sealed, opaque envelopes. According to the sample size calculation, 50 participants will be allocated to each group, hence 100 identical A5 envelopes have been sealed – each containing a folded note whereupon either “*operative”* or “*conservative”* is written. In order to assure similar timewise enrolment the following measures will be applied (Fig. 2). The 50 envelopes for operative treatment will be packed into stacks of 5 envelopes. The same will be done with the 50 envelopes for conservative treatment. One stack of each treatment arm will be mixed resulting in an equal chance to draw either treatment or intervention among the ten envelopes. The including health care personnel will draw one of the 10 envelopes and hence allocate the participant randomly to either treatment arm 1 or 2. When there are only three envelopes left, one stack of each group will be opened and mixed into the remaining. By this measure, the health care personnel cannot predict the allocated treatment based upon the order of previous mixed treatment allocation from the mixed pool of small envelopes.

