### Statistical plan and analysis

#### Sample size

The sample size was calculated based on a 20% difference in complication rate between the two treatment groups, an alpha level of 5% and a power of 80%. Consequently, each group shall at least consist of 49 participants. The control group was decided to be of equal size.

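### Telephone recruits sign written consent after randomisation, at a time that depends on the arm drawn, so allocated patients who never sign could be lost unequally between the arms

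*Protocol article*

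**What the plan says.** The Recruitment section of the protocol article describes two routes into the trial. The main one is the emergency room: "Patients are primarily recruited by directly contact in the emergency room on the day of primary contact", with written consent asked for there. The second picks up patients at the next day's conference, so that each is "offered enrollment in the study either directly in the emergency room or the day after by telephone". On the telephone route, "written consent is obtained before surgery or at the 2 week out-patient visit, if the participant should be randomly assigned to conservative treatment". The section closes with "The recruiting health care personnel randomly assigns participants to the interventions as described below".

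Four other places bear on this:
- **Randomization:** "50 participants will be allocated to each group, hence 100 identical A5 envelopes have been sealed".
- **Sample size:** "each group shall at least consist of 49 participants".
- **Discussion:** "Practical limitations prevent the conduction of a double-blinded data collection, as no sham operations will be performed", so patients know which treatment they receive.
- **Table 1:** the 2-week visit is the first assessment after the day of injury for complications, Quick DASH and pain at rest.

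**The concern.** A signing time that differs by arm can be applied only once the arm is known. On the telephone route the draw therefore comes before the signature. Until the signature, a patient who agreed orally can still decline to sign, knowing the allocation. In the cast arm this open period runs to the 2-week visit, so the patient has also had two weeks of the treatment. In the operative arm it closes before the operation.

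If some allocated patients never sign and their data cannot be used, the groups compared are no longer the groups randomised. The reasons for not signing may differ by arm and may relate to early complications, which are part of the primary outcome. Last observation carried forward, which the statistical analysis plan section prescribes for lost data, does not help if none of a patient's data may be used. At stake is the randomised comparison of complication rates, on which the trial's hypothesis of fewer complications in plaster is tested.

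**Working it through.** **1. Order of events, from the text**

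| Route and arm | Written consent | Arm known when signing? | Treatment experience before signing |
|---|---|---|---|
| Emergency room | Asked for at first contact | The rule does not depend on the arm | None |
| Telephone, operative | Before surgery | Yes | No surgery yet |
| Telephone, cast | 2-week visit | Yes | About two weeks in plaster |

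The two telephone rows follow from the rule itself and need no assumption.

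**2. Margin in the sample size**

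The plan has 50 envelopes per arm and needs at least 49, so the margin is 50 − 49 = 1 patient per arm. The plan gives a difference of 20 percentage points, two-sided alpha of 5% and power of 80%, but no rate per arm. A two-sided test of two proportions with pooled variance and no continuity correction gives 49 per arm at 25% against 5% (assumed rates). Power is then 0.801 at 49 per arm and 0.809 at 50.

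**3. Loss of power**

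Cast patients lost = 50 × telephone share × proportion not signing. Neither factor is in the article, so both are varied.

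| Telephone share (assumed) | Not signing (assumed) | Cast patients lost | Power, 25% v 5% |
|---|---|---|---|
| 10% | 5% | 50 × 0.10 × 0.05 = 0.25 | 0.808 |
| 20% | 20% | 50 × 0.20 × 0.20 = 2.0 | 0.799 |
| 50% | 30% | 50 × 0.50 × 0.30 = 7.5 | 0.767 |

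Even the worst case costs about 4 points of power.

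**4. Possible bias**

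Assume a true complication rate of 15% in both arms, so 50 × 0.15 = 7.5 expected events in the cast arm.

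| Cast patients lost | All had a complication | None had a complication |
|---|---|---|
| 3 | (7.5 − 3)/47 = 9.6% | 7.5/47 = 16.0% |
| 5 | (7.5 − 5)/45 = 5.6% | 7.5/45 = 16.7% |

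The extremes run from an apparent gain for the cast of 9.4 points (15 − 5.6) to an apparent harm of 1.7 points (16.7 − 15). The sign depends on who fails to sign, which the article cannot tell us.

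**5. Effect on the test, as illustration only**

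These are two-sided Fisher exact tests, operative against cast. The 14% in the cast arm (7/50) and the 36% in the operative arm (18/50) are the earlier trial's rates quoted in the Discussion. The 15/50 is an assumption chosen close to the 5% limit.

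| Scenario | Counts | p |
|---|---|---|
| Nobody lost, 15 operative events | 15/50 v 7/50 | 0.090 |
| One cast patient with a complication lost | 15/50 v 6/49 | 0.048 |
| Two cast patients with a complication lost | 15/50 v 5/48 | 0.023 |
| Two with a complication lost in each arm | 13/48 v 5/48 | 0.065 |
| Two cast patients without a complication lost | 15/50 v 7/48 | 0.091 |
| Nobody lost, earlier trial's rates | 18/50 v 7/50 | 0.020 |

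One or two selective losses can change the conclusion when the result is already near the limit. They need not change it otherwise.

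**The case against.** The strongest reply is that signing is not the same as deciding. Someone offered enrolment by telephone and then randomised has presumably agreed orally first, and a condensed article may leave the recording of that agreement to the full protocol. This stands: a reader might infer that patients are randomised without having agreed at all, and the text does not support that. Oral agreement does not, however, make the signing times equal.

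Second, a reader might infer that non-signers are dropped from the analysis. No section says so. The abstract promises an intention-to-treat analysis (the statistical analysis plan section says only that it will be considered), and Data management describes active follow-up of patients who miss visits. What remains is that the article fixes the late signature without fixing how non-signers are counted.

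Third, a reader might infer that the bias favours the cast. That is not established. A cast patient with early trouble has good reason to attend the 2-week visit, and patients unhappy with their arm can leave any open trial. The difference is that a patient who signed first and then withdraws can normally still be counted with the data collected so far, whereas one who never signed may not be.

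Two further inferences fail. Capacity to consent need not wait for the signature: a physician approves eligibility, and these patients were already seen in the emergency department. The control arm's signature at 2 weeks does not touch the randomised comparison, because that arm is not randomised and is published separately.

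**Conclusion.** The point holds in limited form. For telephone recruits, the Recruitment section places the signature after randomisation and at different times in the two arms, in a trial where patients know their treatment. This is a stated rule, not a detail left out. It opens a way to lose patients after randomisation and unequally by arm.

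The size cannot be derived from the article, because the telephone share, the proportion who do not sign and their outcomes are all unknown. The emergency room is the main route, so the number may be small. Loss of power is minor over the whole assumed range. Bias could matter with only a few selective losses, in either direction. The p-values show sensitivity under chosen counts and do not predict the result: with the earlier trial's own rates, the comparison is significant with nobody lost.

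**What to change.** In the Recruitment section, state that no envelope is drawn until written consent is signed, electronically or in person, by the same rule for both arms. Someone reached by telephone who does not sign is then simply not randomised.

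For patients already randomised by telephone, report by arm how many never signed. Keep all randomised patients in the intention-to-treat analysis as far as consent allows.

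The cost is a protocol amendment, an electronic form or a short attendance for telephone recruits, and some contacts lost before randomisation. Those losses slow recruitment a little but cannot bias the comparison between arms. The sample size and the treatments do not change.
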